**Detailed Protocol:**

**“Modifying the Workplace to Decrease Sedentary Behavior and Improve Health”**

**I. Background and Significance**

Prolonged sedentary behavior characterized by long bouts of sitting increases the risk for premature mortality and chronic health hazards including obesity, diabetes, cardiovascular disease, cancer and musculoskeletal disorders.[^1-8^](#_ENREF_1) This increased risk is present even among individuals who regularly engage in moderate-vigorous physical activity.[^6^](#_ENREF_6)^,^[^9^](#_ENREF_9) More than 50% of the American workforce is employed in office jobs involving prolonged sitting and are therefore at risk for these health hazards.[^10^](#_ENREF_10) Ergonomic sit-to-stand and dynamic treadmill workstations are innovative workplace interventions that allow office workers to decrease sedentary behavior and engage in light activity and standing while working.

Our preliminary 9-month trial examining the feasibility of using treadmill workstations at the workplace demonstrated that providing overweight office workers (N=12) with these dynamic workstations reduces sedentary behavior and improves overall health.[^11^](#_ENREF_11) After 3 months, participants self-selected to replace an average of 2.5 hours of sitting with 74 min of slow walking and 82 min of standing at the treadmill workstation. Workstation use declined after nine months because we did not implement any strategies to sustain this behavior change. On average, participants’ decreased weight by 2.5 + 3.9 kg and significantly reduced waist and hip circumference, total cholesterol, low-density lipoproteins and glycosylated hemoglobin. Alkhaja et al. reported that sedentary office workers using sit-to-stand workstations reduced their average sitting time by 2.3 hours during the workday and marginally improved cholesterol levels.[^12^](#_ENREF_12) In addition, Pronk et al.[^13^](#_ENREF_13) and Hedge et al.[^14^](#_ENREF_14) reported that using a sit-to-stand workstation to replace approximately 60 min of sitting with standing daily for 7 weeks significantly reduces upper back and neck pain and overall fatigue. Using sit-to-stand workstations also makes users feel more healthy, energized focused and happy.[^13^](#_ENREF_13) These data establish the feasibility of modifying the workplace using treadmill and sit-to-stand workstations to improve health.

Although prospective evidence emphasizes a reduction in sitting time to improve health, there is minimal experimental evidence demonstrating the benefits of reducing workplace sitting using treadmill and sit-to-stand workstations, which are popular alternatives to decrease workplace sitting. Only one study suggests that modifying the physical office-environment using treadmill workstations improves measures of adiposity, total cholesterol, and long-term glycemic control.[^11^](#_ENREF_11) It is not known if accumulating light intensity activity throughout the workday using treadmill workstations decreases musculoskeletal discomfort and perceived job stress. While replacing sitting with standing at work using a sit-to-stand workstation improves musculoskeletal discomfort and mood,[^13^](#_ENREF_13)^,^[^14^](#_ENREF_14) there is minimal empirical evidence demonstrating that using sit-to-stand workstations benefits cardiovascular and metabolic health. It is also necessary to compare the effects of using treadmill and sit-to-stand workstations on health because the physiological processes activated during slow walking and standing are not the same. For instance, treadmill workstations allow users to increase energy expenditure through dynamic muscular contractions, which is absent when standing (sustained static muscular contractions) at sit-to-stand workstations.[^15^](#_ENREF_15) However, sit-to-stand workstations may yield larger and sustainable decreases in workplace sedentary behavior than treadmill workstations and produce comparable health benefits over time. The abovementioned research gaps need to be examined using a robust and high-quality study methodology.

This project will provide empirical evidence on the effect and sustainability of treadmill and sit-to-stand workstations as novel ways to reduce sedentary behavior in seated office workers. A significant contribution of our project will be the development of optimal evidence-based strategies and recommendations to modify the office environment to decrease workplace sedentary behavior. The long-term benefit of decreasing workplace sedentary behavior is a significant reduction in chronic cardio-metabolic and musculoskeletal illness among employees. Employers may adopt these strategies to improve employee wellbeing and help control the growing prevalence of chronic health problems.

**II. Specific Aims**

The primary objective of this project is to determine the effects of decreasing sedentary behavior at work by at least 3hrs/day using treadmill (walking and standing) and sit-to-stand (standing only) workstations on the health of overweight office workers. Our central hypothesis is that decreasing sedentary behavior at work using these workstations will improve overall health in study participants.

**Aim 1:** **To** **conduct a 12-month, cluster-randomized trial with an intent-to-treat design to determine the effects of using treadmill and sit-to-stand workstations at the workplace on health variables in overweight office workers (N=66) with seated desk jobs.**

*Approach:* We will measure the following variables at baseline and/or after 3, 6, and 12 months: (a) anthropometrics (weight, waist and hip circumference) and body composition (b) blood-flow hemodynamics, (c) psychological affect, (d) job stress and (e) musculoskeletal discomfort. Blood biomarkers including fasting plasma glucose, HBA1C, and lipids will be measured at baseline and after 12 months.

All volunteers will attend a 30-min face-to-face information session at baseline on strategies and benefits of reducing workplace sedentary time and will be trained on office ergonomics to reduce musculoskeletal discomfort. We will then cluster randomize volunteers into a treadmill workstation (N=22), sit-to-stand workstation (N=22) and a control group (N=22). At an organizational level, department supervisors will be trained on the benefits of reducing workplace sedentary behavior and on strategies that encourage employees to sustain positive behavior change.

*Hypothesis*: We hypothesize that improvements in health variables for the sit-to-stand group will be significantly lower than the treadmill workstation group, but higher than the control group during follow-up.

**Aim 2:** **To compare the efficacies of treadmill and sit-to-stand workstations in decreasing workplace sedentary behavior.**

*Approach:* Based on our preliminary work using treadmill workstations, we will recommend a minimum use of 3 hours/day for the treadmill (walk: 2hrs and stand: 1hr) and sit-to-stand workstations. We will use accelerometers to measure time spent sitting, standing and in activity for 1-week at baseline and after 3, 6, 9 and 12 months.

*Hypothesis 2A*: Decrease in sedentary behavior will be greatest in the sit-to-stand group and lowest in the control group.

*Hypothesis 2B*: Based on our preliminary work, we postulate that decreasing workplace sedentary behavior in the intervention groups will not result in a compensatory increase in sedentary behavior outside the workplace.

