**Activity monitoring:** This measurement will be conducted for a period of 1 week. Participants will be asked to wear 2 small activity monitors (53 x 35 x 7 mm, weight=15 grams), one on the right thigh and the other on the torso (chest or abdomen). The device will be attached to the skin using medical grade, hypoallergenic tape or soft elastic bands. We will measure time spent at work and outside the workplace for one week using radio frequency identification technology (RFID). A thin RFID sticker tag (120 mm x 44 mm x 0.4 mm) will be wrapped around the activity monitor on the torso. This will record every time a participant enters and leaves their place of work on an RFID reader installed in the building. During this 1-week period, participants will record the times they wore and removed the monitors and the times they arrived and left their workplace. Based on the data collected using these devices, participants will be provided with retrospective feedback every 3 months on their activity behavior.

d) Procedures/surgical interventions, etc.

N/A

VI. Biostatistical Analyses

a) Specific data variables being collected during the study (e.g., data collection sheets)

Please see attached data collection forms:

1. Data collection sheet
2. Monitor log
3. Health History Questionnaire
4. Brief Block Food Questionnaire
5. Ergonomic measurements
6. Modified National Institute of Occupational Safety and Health Generic Job Stress Questionnaire
7. Positive and Negative Affect Schedule
8. Musculoskeletal Discomfort questionnaire

b) Statistical methods

Aim1: Hypothesis testing will entail an intent-to-treat two-tailed design with a nominal type I error of 0.05.  Preliminary descriptive analyses will explore observed differences in subject characteristics that may be related to study outcomes between the three groups. Variables with notable differences will be included in multivariable models. Mixed linear regression models will be used to compare differences between groups across all measurement points.  These models will include variables identified in the preliminary analyses as potential confounders.

Aim2: We will use mixed linear regression models to examine within and between-group differences in the total time spent in sedentary behavior, sitting, standing, and walking while at work and outside the workplace.

c) Power analyses

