Sample size calculations are based on body weight change among participants (N=12) in our preliminary study.[^11^](#_ENREF_11) Our current study will have 22 participants in each of the three study arms. This will provide sufficient power to detect an effect size of 0.89 between each of the groups where the effect size = Δ/s (Δ: mean difference between two groups; s: common standard deviation). A standard deviation of 3.9 kg for weight observed in our pilot study corresponds to a mean detectable difference of 3.5 kg between groups. Although we anticipate minimal clustering within the departments at the study site, the power estimates presented above are based on an effective sample size of 60 subjects reflecting an intra-class correlation coefficient of 0.01. Comparisons between the most effective intervention and the control group will have substantially greater power reflecting larger differences in mean measurements.

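### Hypothesis 2B claims that sitting outside work will not rise, but the stated Aim 2 analysis only looks for differences and sets no criterion that could support absence

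*Protocol*

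**What the plan says.** Under II. Specific Aims, Hypothesis 2B postulates, from preliminary work, that "decreasing workplace sedentary behavior in the intervention groups will not result in a compensatory increase in sedentary behavior outside the workplace". Aim 2 schedules one-week accelerometer recordings at baseline and after 3, 6, 9 and 12 months.

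Under VI. Biostatistical Analyses, b) Statistical methods, the whole analysis for Aim 2 is one sentence: mixed linear regression models will "examine within and between-group differences in the total time spent in sedentary behavior, sitting, standing, and walking while at work and outside the workplace". The same sentence serves Hypothesis 2A, which does predict differences. The error rate and sidedness, an "intent-to-treat two-tailed design with a nominal type I error of 0.05", are stated under Aim 1 only.

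Under c) Power analyses: "Sample size calculations are based on body weight change among participants (N=12) in our preliminary study". There are 22 participants per arm, and power rests on an "effective sample size of 60 subjects reflecting an intra-class correlation coefficient of 0.01". Nothing is sized for sedentary time. The protocol names no largest acceptable increase, no equivalence or non-inferiority test and no confidence-limit rule for 2B.

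**The concern.** 2B is a claim that an effect is absent. A model that looks for differences can contradict it, by showing a clear increase outside work. The only thing such an analysis offers in its favour, as written, is failure to find a difference. That failure becomes more likely as the data become fewer or noisier, so a weaker trial would seem to support 2B more easily.

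At stake is the net effect of the workstations. The protocol goes to some length to separate work from non-work time (two activity monitors and an RFID tag), and it hopes to give recommendations that employers may adopt. If part of the workplace gain is lost at home, the net reduction in sitting is smaller than the workplace figure suggests. A report of no compensation could stand beside data that allow a good deal of it.

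**Working it through.** **Inputs**
- From the protocol: 22 per arm in three arms; effective total 60, hence 20 per arm; ICC 0.01; detectable effect 0.89 SD; weight SD 3.9 kg; recommended workstation use of 3 h/day.
- Assumed: two-sided 0.05 also applies to Aim 2; the effective sample size, given for weight, also applies to sedentary time.
- Not in the protocol: the SD of change in sedentary time outside work. Results are therefore in SD units first.

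**1. The plan's own figure**
- Standard error of a pairwise difference, in SD units: √(2/20) = 0.316.
- Detectable effect at 80% power: (1.960 + 0.842) × 0.316 = 0.886, close to the stated 0.89. In kg, 0.89 × 3.9 = 3.47, the stated 3.5.
- Power at 0.89 SD is 80.4% (normal approximation) or 78.3% (t). The figure reproduces if the unstated power was 80%.
- Design effect: 66/60 = 1.10 = 1 + (m − 1) × 0.01, so m = 11 per department.

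**2. Precision available for 2B** (95% CI half-width)
- One intervention arm against control: 1.96 × √(2/20) = 0.62 SD (0.64 with t).
- Both intervention arms pooled against control, 40 v 20: 1.96 × √(1/40 + 1/20) = 1.96 × 0.274 = 0.54 SD.
- If a department supplied all 22 in an arm, the design effect would be 1 + 21 × 0.01 = 1.21, the effective total 66/1.21 = 54.5 (18.2 per arm), and the pairwise half-width 1.96 × √(2/18.2) = 0.65 SD.

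**3. How often a real increase would be non-significant** (pairwise, 20 per arm, t-based)

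| True increase | Power | Non-significant |
|---|---|---|
| 0.3 SD | 15% | 85% |
| 0.5 SD | 34% | 66% |
| 0.8 SD | 69% | 31% |

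Pooled 40 v 20, normal approximation, at 0.5 SD: Φ(0.5/0.274 − 1.96) = Φ(−0.13) = 45% power, so about 55% non-significant.

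**4. What a margin-based reading could show** (one-sided 0.025, true difference zero)
- With 20 per arm and 80% power, the smallest increase that can be excluded is 2.802 × 0.316 = 0.89 SD.
- A 0.5 SD margin needs 2 × (2.802/0.5)² = 62.8, or 63 effective per arm. Power with 20 per arm is Φ(0.5/0.316 − 1.96) = 35%.

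**5. In minutes, for illustration only**
For an assumed SD of 60 to 120 min/day, the pairwise half-width is 0.62 × 60 = 37 to 0.62 × 120 = 74 min/day. That is 21% to 41% of the recommended 180 min/day. At an SD of 90, a true 30 min/day increase (0.33 SD) would be non-significant about 82% of the time: power is Φ(0.333/0.316 − 1.96) = 18%.

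Steps 2 to 5 treat the outcome as one change score per person. Using all four follow-ups may narrow the intervals; the protocol gives no within-person correlation from which to say by how much.

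**The case against.** The strongest reply is that the protocol draws no false conclusion. It says that it postulates no compensation and that models will examine differences. It does not say that a non-significant difference will confirm 2B. A reader might infer that it will, but that rule is not in the text. What stands against the plan is narrower: it names a hypothesis of absence and an analysis for it, and the pair contains nothing else that could count as support.

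A second reply is that a statistical analysis plan could add the margin. It could. But the protocol itself fixes both the hypothesis and its analysis, and judging 2B by a confidence limit is a better method rather than a missing detail.

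Third, the mixed model is sound. This is right: it yields the intervention-minus-control estimate and interval that 2B needs. A reader might go further and say that the trial cannot address compensation at all. That is too strong, since the plan can contradict 2B if a clear increase appears and can report how much compensation the data allow.

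Fourth, 2B speaks of the intervention groups, so change within them seems relevant. It is, as description. But counselling, repeat sessions and three-monthly activity feedback are planned for participants in general, and controls are advised to take three short walks in the workday. A flat trend within an arm could therefore hide compensation offset by these measures.

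Last, the minute figures rest on an assumed SD, and pooling or repeated measures would improve on 0.62 SD. Both points stand; pooling alone leaves 0.54 SD.

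**Conclusion.** The point holds as one of moderate severity on a secondary hypothesis. As written, 2B can be contradicted, but the plan gives no criterion that would support it, and at this size a non-significant result would not do so. Pairwise, the interval reaches about 0.62 SD either side (0.54 SD pooled), and a true 0.5 SD increase would be missed about two times in three (a little over half the time if pooled).

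These figures rest on the protocol's effective 60 participants, on two-sided 0.05 carried over from Aim 1, and on no gain from repeated measures. The minute figures also need an SD that the protocol does not give.

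The point does not reach the main conclusions: the primary objective is health effects, and the sizing is on body weight. Neither Aim 1 nor Hypothesis 2A is affected.

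**What to change.** - Keep the mixed model. State that 2B is judged on the intervention-minus-control change in sedentary time outside work, and say whether the intervention arms are taken separately or pooled.
- Conclude that there is no meaningful compensation only if the upper 95% confidence limit of that contrast lies below a margin that the investigators justify and fix in advance. A natural form is a fraction of the workplace reduction. As an illustration only, a quarter of the recommended 3 h/day is 0.25 × 180 = 45 min/day, which is 0.5 SD if the SD is 90 min/day. If the fraction is applied to the observed reduction instead, the uncertainty of that reduction must be carried into the limit.
- If the limit exceeds the margin, report the interval and claim neither absence nor presence of compensation on that ground.
- Treat within-group change as descriptive only.

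The cost is a few lines of protocol text and the work of justifying a margin; no added data are needed. The downside is that 2B may well end as inconclusive: at a 0.5 SD margin the pairwise chance of a positive conclusion is only about 35%, even if there is no compensation at all.

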**III. Subject Selection**

a) Inclusion and Exclusion criteria

1. Participants have a body mass index greater than 25 kg/m^2^
2. Do not engage in any structured physical activity for more than 2 days/week
3. Are employed in a seated desk job
4. Are free of limitations that prevent walking and standing in bouts lasting 40 to 60 min.
5. Women who are pregnant.

b) Source of subjects and Recruitment methods

Sixty-six participants will be recruited from the Massachusetts General Hospital and Northeastern University. Potential departments at Massachusetts General Hospital include The Cancer Center (protocol office and call center), Professional Billing Office, Materials Management Customer Service, Health and Information Services, Radiology Service Center, and Research Management. Departments at Northeastern University include Speech-Language Pathology Clinic, Department of Communication Sciences and Disorders, Bouve College Office of Research, The John O'Bryant African American Institute, and Northeastern University Humanities Center. These departments were previously identified as potential sites after informal communication about the study with the department heads and human resource management.

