**IV. Subject Enrollment**

a) Methods of enrollment, including procedures for patient registration and/or randomization

A trained project manager will meet potential participants as a group during department meetings and verbally explain study procedures and inclusion criteria. Eligibility will be assessed based on self-report and measured height and weight. If employees from a department express interest in the study, the department will be cluster randomized into either the treadmill workstation, sit-stand workstation, or control group after completing informed consent procedures. Twenty-two volunteers will be randomly selected from each department group. In the event of insufficient volunteers in a group, the project manager will approach other departments to solicit study participation. Our recruitment target will include at least 50% women and 20% minorities, respectively. However, the study design may limit our ability to effectively recruit these two categories of participants.

b) Procedures for obtaining informed consent (including timing of consent process)

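### Criterion 3 neither excludes current users of a sit-to-stand or treadmill workstation nor requires enough desk sitting to replace, so people with little room to change can enter the intervention arms

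*Protocol*

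**What the plan says.** Section III of the Protocol lists five criteria. The one that concerns work is "Are employed in a seated desk job", and the term is not defined further. The neighbouring criterion, "Do not engage in any structured physical activity for more than 2 days/week", concerns exercise and says nothing about sitting at work. Section IV states how eligibility is checked: "Eligibility will be assessed based on self-report and measured height and weight".

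The target change is stated in Section II, where the primary objective is to "determine the effects of decreasing sedentary behavior at work by at least 3hrs/day" by means of the two workstations. Under Aim 2 the investigators add: "we will recommend a minimum use of 3 hours/day for the treadmill (walk: 2hrs and stand: 1hr) and sit-to-stand workstations". Sitting time is measured by accelerometer for one week at baseline and again during follow-up, but no baseline value is made a condition of entry. Section I says of the two workstation types: "which are popular alternatives to decrease workplace sitting". Section VI sets an intent-to-treat analysis at a two-sided 0.05 level.

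**The concern.** The objective presupposes two things about each participant in an intervention arm: at least 3 hours of workplace sitting to give up, and a workstation that is new to them. Criterion 3 secures neither. A person with a mixed role or short desk hours, or one who already stands at an adjustable desk, can truthfully report a seated desk job and pass the screen.

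Once allocated to an intervention arm, that person has less change to show in sitting time (Aim 2), and probably less in the health variables expected to follow from it (Aim 1). Intent-to-treat rightly keeps the person in the analysis. The arm's mean change is then pulled towards that of control. The gap can be closed only at entry, and eligibility belongs in the protocol, so it is not a matter left to an analysis plan.

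**Working it through.** **1. Is the gap closed elsewhere?** The places where it could be closed are these:

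- The other criteria in Section III cover body mass index, structured exercise, ability to walk and stand, and pregnancy. None concerns desk hours or existing equipment.
- The Section IV screen uses self-report and measured height and weight. It adds no condition to those in Section III.
- Baseline accelerometry (Section II, Aim 2) would reveal low sitting but does not gate entry.
- The workstation measures in Section V are tied to installation of the study workstation, so they do not screen for earlier use.
- Adjustment for notable baseline differences (Section VI.b) can balance the groups. It cannot create a response that a participant has no room to make.

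The gap therefore stands.

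**2. Reproduce the plan's own figure.** Inputs from Section VI.c: 22 per arm, effective total 60 (20 per arm), intra-class correlation 0.01, detectable effect 0.89 SD, SD 3.9 kg, difference 3.5 kg. The level is two-sided 0.05 (Section VI.b). No power figure is given, so 80% is assumed.

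- Effective total: 66 / (1 + (m − 1) × 0.01) = 60 when m = 11 per department.
- Detectable effect: (1.960 + 0.842) × √(2/20) = 0.886, which agrees with 0.89.
- In kilograms: 0.89 × 3.9 = 3.47, which agrees with 3.5.
- Power at 0.89: Φ(0.89 × √(20/2) − 1.96) = Φ(0.85) = 80.4%. A noncentral-t calculation gives 78.3%.

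The stated figure reproduces at 80% power, with almost nothing to spare.

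**3. Illustrate the attenuation.** Let f be the share of an intervention arm that shows no response at all, and keep the SD unchanged. The effect against control becomes (1 − f) × 0.89. The values of f are assumptions, since the document supplies none. For scale, 2 of 22 is 9% and 4 of 22 is 18%.

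| f | Effect (SD) | Difference (kg) | Power, normal | Power, t | Effective n per arm for 80% |
|---|---|---|---|---|---|
| 0 | 0.890 | 3.47 | 80.4% | 78.3% | 20 |
| 5% | 0.845 | 3.30 | 76.2% | 74.1% | 22 |
| 10% | 0.801 | 3.12 | 71.7% | 69.4% | 25 |
| 20% | 0.712 | 2.78 | 61.5% | 59.3% | 31 |

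**4. Relax the zero-response assumption.** If affected participants show half the full effect, the mean becomes (1 − f/2) × 0.89. At f = 20% that is 0.90 × 0.89 = 0.801, the same as the 10% row, so power is about 72%.

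The table concerns body weight, the only variable for which the protocol gives a sample size basis. No detectable effect is stated for sedentary time, so the attenuation for Aim 2 cannot be put in the same terms.

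**The case against.** The best reply is that the target population is plain enough. The protocol describes office workers with seated jobs, and the departments were identified after contact with their heads and human resource management. They include a call center and a billing office, where sitting is likely to be long. Baseline accelerometry would also expose low sitters. All of this lowers the likely share of affected people. None of it keeps such a person out.

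The 3 hours is also a recommended minimum, not a threshold for response. Pilot participants replaced 2.5 hours on average and still reported health improvements (Section I). So little room to change does not mean no response, and the zero-response rows of the table are the pessimistic end. This part of the objection stands. So does a second point: 0.89 SD is given as a detectable effect, not an expected one, so the power figures also assume that the truth happens to equal it.

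Four stronger readings are tempting, and the document does not support them:

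- A reader might infer that the contrast *is* diluted. No prevalence of low sitters or existing workstation users is given, so only a possibility can be claimed. Calling the workstations popular does not show that anyone in the listed departments has one, and the protocol also calls them innovative and novel.
- A reader might infer that existing users contaminate the control arm. Outcomes run from baseline, and the sample size rests on weight change. A long-standing user in control has the same exposure at both ends and should show about as little change as any other control. Only a very recent adopter would differ.
- A reader might infer from the listed Speech-Language Pathology Clinic that clinicians who mainly see clients would qualify. The protocol does not describe roles there, and such a person is not in a seated job on an ordinary reading.
- A reader might infer that every part-time employee lacks headroom. Someone who works full days on fewer days per week has ordinary daily sitting.

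**Conclusion.** The point holds as a loosely fixed eligibility criterion; it is not an error or a contradiction. Criterion 3 does not exclude current users of a study-type workstation and does not ask for enough desk sitting to allow the reduction named in the primary objective. No later step repairs this. The consequence is a possible weakening of the contrasts for Aims 1 and 2, arising through the intervention arms.

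The size is unknown. The fall from about 80% to 72% or 61% rests on five assumptions: 10% or 20% affected, no response at all in those people, a true effect of exactly 0.89 SD, an unchanged SD, and an inferred starting power of 80%. Partial response or a smaller share would make the loss smaller. The change is worth making because the calculation has no reserve and prevention costs very little. It is a cheap improvement.

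**What to change.** Extend criterion 3 with two conditions:

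- *does not currently use a sit-to-stand or treadmill workstation at work*;
- a self-reported usual desk-sitting time per workday clearly above the 3 hours to be replaced, with the exact floor set by the investigators, since the document offers no basis for a particular value.

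Ask both in the self-report screen that Section IV already describes, before the department is allocated, so that the answers cannot depend on the arm. There is no need to require a non-adjustable desk: that would turn away people who own an adjustable desk but never raise it.

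The cost is an amended criterion, two screening questions and a slightly smaller pool of volunteers per department. Section IV already allows further departments to be approached if volunteers run short. The results would apply a little more narrowly, to office workers who sit for long periods and do not yet use such a workstation, which is the group the objective addresses.
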